## Abstract

**Background:**

Osteoarthritis (OA) is a highly prevalent and disabling disease. It is estimated that by 2030 the prevalence of symptomatic OA could reach 30 % of the population above 60 years. This randomised controlled trial will investigate the effect of low-level laser therapy (LLLT) and static stretching exercises, as monotherapy and in combination, on pain, quality of life, function, mobility, knee range of motion (KROM) and hamstring shortening in participants with knee OA.

**Methods:**

This study will involve 145 people aged 50–75 years with symptomatic-radiographic knee OA. It will consist of two types of treatments: Low-level laser therapy (LLLT) and stretching exercises. The patients will be randomly allocated to five groups LLLT_ACTIVE_+Stretch, LLLT_PLACEBO_+Stretch, Stretch, LLLT and Control (*n* = 29 each). Treatment frequency will be three sessions/week for all active groups. LLLT will involve the use of a Gallium-Arsenide laser (904 nm, 40 milliwatts, 3 J/point, 27 J/knee) over 24 sessions for the monotherapy group and 9 sessions for the LLLT+Stretch groups. Stretching will consist of seven exercises completed over 24 sessions. The control group will receive a booklet. Participants will be treated for 2 months (Stretch, LLLT and Control groups) or 3 months (LLLT + Stretch groups). Participants and the outcome assessor will be blind to treatment allocation throughout the study.

The primary outcome is pain measured by Visual Analogue Scale. Secondary outcomes include quality of life assessed by Western Ontario and McMaster Universities Arthritis Index, function by Lequesne Algofunctional Index, mobility by Timed Up and Go Test, KROM by goniometry of knee flexion and hamstring shortening by popliteal angle. The statistical method will follow the principles of per-protocol analysis.

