## Methods

### Trial design

This study will be a five-arm randomised controlled trial with blind evaluator.

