### Study procedure

All participants will be screened by an orthopaedist or rheumatologist to diagnose and identify the severity of KOA. The diagnosis will be based on the radiograph analysis and physical assessment and the severity will follow the Kellgren & Lawrence classification. After confirmation of KOA patients will be referred to the local physiotherapy sector. The eligibility criteria will be applied during the prior assessment standardized by the clinic, and when the patient is considered eligible and is interested in participating in the study, their contact (full name and phone number) will be passed to the study assessor in order to schedule the baseline assessment.

Participants will be instructed to bring knee radiographs, prescription medications taken and the referral for physical therapy. Participants will be asked to use comfortable clothes and not to use analgesic or anti-inflammatory drugs 48 h prior the evaluation date, but to continue to perform their ADLs in the usual way. On the baseline visit, the criteria for inclusion and exclusion will be reapplied.

Five intervention groups will be part of the study:LLLT_ACTIVE_ + Stretch: 3 weeks of low intensity laser therapy (LLLT) followed by 8 weeks of stretching exercises.LLLT_PLACEBO_ + Stretch: 3 weeks of placebo LLLT followed by 8 weeks of stretching exercises.Stretch: 8 weeks of stretching exercises.LLLT: 8 weeks of active LLLT.Control: minimal intervention through educational booklet.

This study will be conducted by a trained physiotherapist.

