Nine knee points will be irradiated with LLLT: three on the medial joint line; two on the lateral joint line and four points over the borders of kneecap, as shown in Fig. 1 - Application points of LLLT. Each point will receive energy of 3 J/point for 75 s, with a total dose of 27 J/knee in each session. Thus, the time of application will be approximately 12 min/knee. All participants and the physiotherapist will wear safety goggles to shield their eyes from active laser radiation. For participants in the placebo group, the treatment procedure will be identical but without switching on the machine.

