### Randomisation and allocation concealment

The randomisation schedule will be prepared by a researcher not involved in participant recruitment, assessment or treatment using a computer-generated random numbers table. There will be a 1:1 allocation ratio of participants to each one of the five groups. Randomisation will be conducted by random permuted blocks of same size. Each group will have 29 numbers. The list containing this information will remain with the physiotherapist responsible for the treatment.

A number will be assigned to participants according to the order of their evaluation. This digit will be later located in the list and, thus, the corresponding group will be identified. The assessor will perform the assessment unaware of the group to which each participant will belong. After the initial evaluation, the participant will be informed by the physiotherapist responsible of the type, time and frequency of treatment.

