## Discussion

This paper has presented the protocol for an ongoing randomised controlled trial (RCT) to investigate the effect of low-level laser therapy (LLLT) and static stretching exercises, as monotherapy and in combination, on pain, quality of life, function, mobility, knee range of motion and hamstring length in participants with KOA.

The findings of the study will provide reliable information that will guide the future use of LLLT in patients with KOA since the American Academy of Orthopaedic Surgeons (AAOS) guideline was unable to recommend for or against the use of physical agents [36]. Regardless of the whether the findings of the present study are positive, neutral or negative, the results will be important for guiding evidence based practice. For example, if adding LLLT to muscle stretching program provides greater pain relief and functional improvement than stretching exercises alone, this method could be advised as an effective treatment option for these patients. Conversely, if LLLT does not provide additional incremental or singular benefit then this widely practiced intervention, would have evidence to discourage that practice.

Guidelines and meta-analyses request more RCTs evaluating type, intensity, and frequency of exercise, which may contribute to the knowledge of dose–response relationship as well as to the efficacy of stretching as an exercise modality in persons with knee OA. The European League Against Rheumatism (EULAR) recommendations indicate stretching exercises as an adjunctive treatment [37]. However, to our knowledge, no studies have verified the effectiveness of stretching as monotherapy. This study will contribute with evidences of the use of this modality in clinical practice and will provide additional insights for the conservative treatment options.

It is important to note that the ethics committee did not approve the inclusion of a group with placebo laser as monotherapy, resulting in a study limitation.

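### The abstract says participants are blind throughout, but at best they can be blind to active versus placebo laser in one pair of the five groups

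*Protocol article*

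**What the plan says.** The abstract of the protocol article, under Methods, makes an unqualified claim: "Participants and the outcome assessor will be blind to treatment allocation throughout the study".

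Other sections describe something narrower:

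- Trial design: "This study will be a five-arm randomised controlled trial with blind evaluator". Participants are not mentioned.
- Study procedure lists the regimens. The two combined groups receive "3 weeks of low intensity laser therapy (LLLT) followed by 8 weeks of stretching exercises" and "3 weeks of placebo LLLT followed by 8 weeks of stretching exercises". The other three are stretching alone for 8 weeks and then, in the protocol's words, "8 weeks of active LLLT.Control: minimal intervention through educational booklet".
- Low-level laser therapy (LLLT), on the placebo group: "the treatment procedure will be identical but without switching on the machine".
- Randomisation and allocation concealment: after baseline, "the participant will be informed by the physiotherapist responsible of the type, time and frequency of treatment". Only the assessor is described as unaware of the group.
- Discussion: "the ethics committee did not approve the inclusion of a group with placebo laser as monotherapy", which the article names as a limitation. It does not go back to the blinding claim.

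**The concern.** A participant who attends group stretching, has laser sessions with no exercise, or goes home with a booklet can see which of these it is. Only the active and placebo laser courses before stretching are designed to look the same. The abstract therefore attributes to the whole trial a property that one pair of groups can have.

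This matters because the primary outcome is pain on a visual analogue scale, scored by the participant's own mark. Blinding the assessor does not blind that measurement. Expectation can therefore enter every contrast between visibly different regimens. So can differences in contact: three sessions a week in the active groups, against a booklet and weekly telephone calls in the control group. Someone who reads only the abstract would take all the pain comparisons as participant-blind.

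**Working it through.** **Inputs.** Five groups of 29, 145 in total (abstract; Randomisation and allocation concealment). Regimens from Study procedure and Control. Sample size: a 2-point difference between treatment groups and control, two-sided 0.05, power 80 %, 25 per group before drop-out (Sample size calculation).

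**Step 1. The plan's own total.** 5 × 29 = 145, as stated.

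**Step 2. What a participant can see.**

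| Group | Laser sessions | Stretching | Booklet | Group with the same visible regimen |
|---|---|---|---|---|
| Active LLLT + Stretch | 3 weeks | 8 weeks | no | Placebo LLLT + Stretch |
| Placebo LLLT + Stretch | 3 weeks | 8 weeks | no | Active LLLT + Stretch |
| Stretch | none | 8 weeks | no | none |
| LLLT | 8 weeks | none | no | none |
| Control | none | none | yes | none |

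Three groups have no counterpart: 3 × 29 = 87, and 87/145 = 60 %.

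**Step 3. Contrasts.** Five groups give 5 × 4 / 2 = 10 pairwise contrasts. The visible regimen matches in 1, active versus placebo laser with stretching. It differs in the other 9. Among those 9 are:

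- all 4 contrasts with control, the comparison that the sample size uses;
- active combination versus Stretch and active combination versus LLLT, which correspond to the Background hypothesis that the combination beats either treatment alone.

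**Step 4. How much a reporting bias could matter (illustration only).** The article gives no SD, so 25 per group cannot be reproduced directly. Solving the usual formula backwards gives the SD it implies: SD = 2 × √(25/2) / (1.960 + 0.842) ≈ 2.52 cm. The standard error of a difference between two groups of 25 is then 2.52 × √(2/25) ≈ 0.714 cm. Suppose there is no true effect but unblinded reporting shifts the difference by b. The two-sided rejection rate at 0.05 is 1 − Φ(1.960 − b/0.714) + Φ(−1.960 − b/0.714):

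| Assumed b (cm) | Rejection rate |
|---|---|
| 0 | 0.050 |
| 0.25 | 0.064 |
| 0.50 | 0.108 |
| 0.75 | 0.183 |
| 1.00 | 0.288 |

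Both the SD and the values of b are assumptions; the documents give neither. The blinding contradiction does not depend on this step.

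**The case against.** The strongest defence is that the body of the article never claims blind participants. The trial design section says evaluator only, and the missing placebo-laser monotherapy group was refused by the ethics committee and is disclosed as a limitation. On this view one abstract sentence is wrong, no test or sample size depends on it, and the participants have already finished. Much of this stands. The missing group is not a fault of the plan. The counts of groups and contrasts show where bias can enter, not how large it is. But admitting that limitation does not correct the abstract. This is also not a detail lost in condensing a protocol: it is a positive statement that the article's own text contradicts, and it bears on how the primary outcome may be interpreted.

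Some stronger readings are tempting, and the documents do not support them:

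- *The assessor is unblinded by visit timing.* Assessments follow each intervention, and a fixed 8-week reassessment is given only for the control group. Visits at weeks 3 and 11 in the combined groups would be an inference. Nothing says that the assessor knows when a participant started.
- *The one sham-matched pair is also unblinded.* Participants are told the type of treatment, and the placebo device is not switched on. The article does not say that active or placebo status is disclosed, or that participants could tell. This is a point to clarify, not a demonstrated failure.
- *The Discussion plans to claim a stand-alone laser benefit from an open comparison.* The sentence on stand-alone benefit concerns a null result. Its positive example is adding laser to stretching, for which the design does have a sham-matched pair.
- *Mobility and joint-angle measures are neglected.* Timed Up and Go, knee range of motion and popliteal angle are already secondary outcomes. The first two depend partly on the participant's effort, so they would not replace the pain result.

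**Conclusion.** The point holds as a contradiction in the document. The abstract's claim about participants is not true of this design. Of the 145 participants, 87 (60 %) are in groups without a sham counterpart. Participant blinding is possible in at most 1 of 10 pairwise contrasts and in 0 of the 4 contrasts with control.

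The figure of 1 in 10 is the favourable count. It assumes that active or placebo status is withheld in the two LLLT + Stretch groups and that the sham is not recognised. It does not depend on whether LLLT-alone participants are told that their laser is active: no group receives placebo laser alone, and every possible comparator has a visibly different regimen. The size of any bias in the pain results cannot be derived from the documents. The assessor-blinding half of the sentence is not shown to be wrong.

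**What to change.** 1. Replace the abstract sentence with: *The outcome assessor is blind to allocation; participants are blind only to active versus placebo laser within the two LLLT + Stretch groups.*
2. Reconcile the section on randomisation and allocation concealment with this by stating that, in those two groups, the treatment information given to participants does not reveal active or placebo status, if that is so. If it was revealed, the participant part of the replacement sentence must go as well.
3. Base conclusions on the specific effect of laser on pain on active versus placebo laser with stretching.
4. Report all other pain contrasts, including LLLT versus Control and Stretch versus Control, as open to participants.

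The timeline section says that participants had finished in December 2014 while the analysis was still to be completed, so wording and interpretation can be corrected before results are reported. The price is narrower conclusions. No new data, groups or tests are needed.

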Persons with KOA tend to avoid physical activity in an attempt to prevent pain. It was shown that this behaviour, over time, reduces the strength of knee extensors further impairing ability to perform activities of daily living [20]. When subjected to immobilization or inactivity, the peri articular connective tissue becomes fibrotic, resulting in capsular adherence, adaptive shortening of muscles and consequent limitation of ROM [21] . Studies have reported that individuals with KOA have increased hamstring muscle activity, preventing the joint reaching its maximum extension during the gait cycle, a fact that further compromises knee ROM [22, 23]. Pain and reduced ROM in affected joints are important risk factors for the occurrence of functional disability [24]. It is presumed that stretching performed slowly and sustainably must be performed to change this picture.

Therapeutic exercises have proven to be beneficial for individuals with KOA, however it is unclear which type, frequency and intensity are more suitable. We propose to test muscle stretching in this study in order to ascertain if this type of exercise is appropriate for this population. Despite their relevance, studies testing stretching exercises are scarce.

The combination of these two treatments (LLLT and stretching) aims to relieve pain with the initial use of the laser to enhance the effect and implementation of stretching exercises. Thus, the hypothesis of this study was that LLLT combined with stretching exercises would demonstrate greater benefits for patients with KOA than either treatment alone.

The primary objective of this research will be to investigate the effect of static stretching and LLLT (904 nm), in combination or as monotherapy, in the management of pain in persons with KOA. The secondary objective was to evaluate the influence of each intervention on quality of life, function, mobility, knee flexion range of motion and hamstring length of these individuals compared to a control group.

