### Statistical analysis

All data will be submitted to a descriptive inferential analysis. For adherence to normality, the Kolmogorov-Smirnov test will be conducted. The intergroup comparison will be performed by simple variance analysis (one-way ANOVA) for data with normal distribution and the ANOVA Kruskal-Wallis for non-normal distribution. For statistically significant differences, post hoc tests like Holm-Sidak (parametric) and Tukey test (nonparametric) will be applied. Categorical variables will be compared by chi-square test.

In view of the need to determine clinically important differences, we will calculate the Relative Gain that corresponds to the gain that the patient obtained after the end of treatment relative to how much they could improve. The Average Gain will be calculated for intergroup analysis and will be obtained by the difference between pre and post intervention for each variable. The data will be processed by the software SigmaStat 3.5. The significance level for all analyses will be α = 0.05.

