### Sample size calculation

The primary outcome measure VAS (range: 0–10 cm) was used to estimate the sample size. Using a minimal clinically important change of two-point difference between the treatment groups and control group, with a significance level of 0.05 (2-tailed) and a power of 80 %, we estimated that 25 participants were needed in each group. To allow for a 15 % drop-out rate, we aimed to include 29 participants in each group.

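### Per-protocol is the only analysis principle stated for a superiority trial, so exclusions after randomisation can bias the pain comparison

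*Protocol article*

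**What the plan says.** The abstract (Methods) fixes the principle: "The statistical method will follow the principles of per-protocol analysis". The Statistical analysis section gives the tests ("The intergroup comparison will be performed by simple variance analysis (one-way ANOVA) for data with normal distribution", Kruskal-Wallis otherwise, then post hoc comparisons), the pre-post gains and the significance level. It names no analysis set, does not define the per-protocol set, and mentions no analysis of everyone as randomised.

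The aim is superiority. The Background expects that "LLLT combined with stretching exercises would demonstrate greater benefits for patients with KOA than either treatment alone". The Sample size calculation is built on a difference: "Using a minimal clinically important change of two-point difference between the treatment groups and control group". No non-inferiority or equivalence margin appears anywhere. The endpoint concerned is the main one: "The primary outcome is pain measured by Visual Analogue Scale".

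The arms ask different things of participants (abstract; Study procedure; Interventions). The two combined groups have 9 laser or placebo-laser sessions followed by 24 stretching sessions. Stretch alone and LLLT alone have 24 sessions each. Control has a booklet and weekly telephone calls. Under Assessment procedures, participants in regular use of NSAIDs or OA drugs are told to stop them until the trial ends. Only simple analgesics and thermotherapy are then allowed for pain control.

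**The concern.** In a superiority trial the randomised groups are comparable because nobody is removed for what happens after allocation. A per-protocol analysis removes people for exactly that reason. Two features of this design give grounds to expect that removal will not be neutral.

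First, the number of sessions that can be missed runs from 0 to 33 by arm. It also differs in the contrast that the hypothesis is about: 33 sessions for the combination against 24 for either treatment alone.

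Second, if taking a disallowed drug for pain counts as a deviation, exclusion would depend on the primary outcome itself. The article does not say what counts as a deviation, so the excluded set could also be settled after outcomes are known.

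The Discussion intends the result to guide practice, including discouraging laser use if no benefit is seen. That conclusion calls for an estimate in the groups as randomised.

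**Working it through.** **Inputs from the article.** Difference 2 cm on a 0–10 cm VAS; "with a significance level of 0.05 (2-tailed) and a power of 80" %; 25 per group needed; 29 per group randomised after a 15 % allowance; five equal groups. The article states no SD and no exclusion rates by arm. Those below are assumptions.

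**The plan's own sample size.** For two means, n = 2(1.960 + 0.842)² SD²/2². Setting n = 25 gives SD = 2 × √(25/2)/2.802 = 2.52 cm. With the t distribution, SD = 2.47 cm needs 24.94, so 25. The stated 25 is therefore consistent with an SD of about 2.5 cm, but cannot be reproduced without assuming one. Allowance: 25 × 1.15 = 28.75, rounded up to 29 (dividing instead, 25/0.85 = 29.4, rounded up to 30). Total: 5 × 29 = 145, as stated.

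**Burden.** Combined groups: 9 + 24 = 33 sessions over 3 + 8 = 11 weeks. Stretch: 24 over 8 weeks. LLLT: 24 over 8 weeks. Control: 0.

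**Bias formula.** If retained and excluded participants differ by g cm in mean pain change, with the same g in both arms, then

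net bias = (share excluded in active − share excluded in Control) × g.

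| Active / Control excluded | g = 1 cm | g = 2 cm | g = 3 cm |
|---|---|---|---|
| 15 % / 15 % | 0 | 0 | 0 |
| 15 % / 5 % | 0.10 | 0.20 | 0.30 |
| 15 % / 0 % | 0.15 | 0.30 | 0.45 |
| 25 % / 5 % | 0.20 | 0.40 | 0.60 |

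If Control loses more than the active arm, the sign reverses.

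**Effect on one unadjusted two-arm test.** SE = 2.47 × √(2/25) = 0.699 cm.
- Bias 0.30 cm: shift 0.30/0.699 = 0.43 SE, so P(|Z| > 1.96) = 0.071.
- Bias 0.40 cm: shift 0.40/0.699 = 0.57 SE, so P(|Z| > 1.96) = 0.088.
- With 25 in the active arm and all 29 in Control, SE = 2.47 × √(1/25 + 1/29) = 0.674, and the first figure becomes 0.073.

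**Simulation under no treatment effect** (29 per arm, SD 2.52 cm, 6,000 runs, two-sample t-test at 5 %). ρ is the correlation between staying in the analysis and outcome.

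| Excluded, active / Control | ρ = 0 | ρ = 0.3 | ρ = 0.5 | ρ = 0.8 |
|---|---|---|---|---|
| 15 % / 0 %: error | 5 % | 6 % | 8 % | 12 % |
| 15 % / 0 %: mean bias | 0.00 cm | 0.18 cm | 0.30 cm | 0.50 cm |
| 25 % / 5 %: error | 4 % | 7 % | 9 % | 18 % |
| 25 % / 5 %: mean bias | 0.00 cm | 0.25 cm | 0.40 cm | 0.66 cm |

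With 15 % excluded in both arms the mean bias is about zero at every ρ.

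**The planned sequence of tests** (five groups of 25, SD 2.47 cm, one-way ANOVA and then Holm-Sidak over all ten pairs, 20,000 runs). With 0.30 cm bias in all four active arms, the overall test rejects in about 6.6 % of runs, against about 5.2 % without bias. A given active-versus-Control pair is declared different in about 0.9 %, against 0.5 %. At 0.40 cm the figures are about 7.7 % and 1.2 %.

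**Power after the change.** With all 29 per group measured, SD 2.52 cm and the 2-cm effect undiluted, power for one pair is 85.6 %, against 80.1 % with 25.

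**The case against.** A condensed article may leave analysis sets to a fuller plan. That does not apply here, because the article states the principle positively; a plan with an as-randomised primary analysis would contradict it.

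The stronger objections concern what a reader might infer beyond this:

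- **That bias is certain.** It is not. Bias needs exclusion that is related to outcome and unequal between arms, and the article gives no rates. With ρ = 0, or with equal exclusion and equal gaps, there is none.
- **That it must favour the more demanding arms.** This is not established. The drug restrictions apply to everyone, and Control participants in persistent pain might breach them or leave. That would shrink or reverse the bias.
- **That every contrast is affected by burden.** Active and placebo laser plus stretching have the same 33 sessions, and Stretch and LLLT the same 24. Burden separates active arms from Control and the combination from single treatments.
- **That 7 % is the trial's error rate.** It belongs to one unadjusted comparison. Under the planned ANOVA with Holm-Sidak the absolute rates are smaller, as shown above.
- **That the 15 % allowance ("drop-out rate, we aimed to include 29 participants in each group") leaves out poor adherers.** The article does not define drop-out, so it may include them.

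All these limits stand. They restrict the claim about size and direction; none gives a reason for per-protocol as the only analysis of a superiority question.

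**Conclusion.** The point holds as a criticism of a stated rule. Per-protocol is the only analysis principle given, the trial asks a superiority question, and its arms differ in ways that make unequal, outcome-related exclusion plausible. The pain comparison can therefore be biased by an amount and in a direction that the per-protocol result cannot reveal.

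The article supports no single figure for the size. In the illustration with 15 % of one active arm and none of Control excluded and a 2-cm gap, the bias is 0.30 cm, or 0.30/2 = 15 % of the target difference. The exclusion rates, the gap and the SD are all assumptions. Confidence is high that the choice of population should change, and low about how far the result would move.

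**What to change.** State that the primary analysis includes all randomised participants in the group to which they were allocated, using every measured end-of-treatment VAS regardless of adherence. Name a missing-data method together with its assumption, for example missing at random given arm and baseline VAS, and add a sensitivity analysis to departures from it. Imputation from arm and baseline alone cannot remove drop-out that depends on the unseen outcome. The main gain comes from keeping poor adherers who were measured.

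Keep per-protocol as a secondary analysis with a written definition of the set.

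The Timeline says that participants finished in December 2014 and that analysis should be complete by the end of August 2015. It does not say whether analysis has started. If it has, date and disclose the change.

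The cost is a paragraph of text, a little more analysis work and possibly a smaller estimated effect. On the plan's own effect size no larger sample is needed, provided outcomes are obtained for all and non-adherence does not dilute the effect.
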